## Abstract

Transcatheter aortic valve implantation (TAVI) has become the standard of care for elderly patients with aortic stenosis. International guidelines recommend that TAVI should be performed only in centers with on-site cardiac surgery (CS). However, rapidly evolving TAVI technology and increasing operator expertise have significantly reduced peri-procedural complications, including those requiring rescue surgery, which occur in less than 0.5% of cases. Furthermore, only a minority of major complications are treated with CS, and the outcomes remain unfavorable. TAVI in centers without CS could represent a solution to reduce waiting times and ensure continuity of care for fragile patients. “TAVI at Home” is a single-arm prospective interventional study. According to sample size calculations based on literature data, the study aims to enroll a total of 200 patients, beginning with a run-in phase of 20 patients to establish safety. The primary endpoint is 30-day all-cause mortality. Secondary endpoints include technical success and the evaluation of single complications 30 days after the procedure. Hospitals without CS that are eligible to perform TAVI must have a high volume of coronary percutaneous interventions, operators with established TAVI experience, collaboration with vascular surgeons, and regular Heart Team meetings to ensure rigorous patient selection.

## 1. Introduction

Aortic stenosis (AS) is the most common valve disease in industrialized countries [1], affecting approximately 5% of adults over the age of 65 years [2], and it is invariably progressive. If untreated, the survival rate is approximately 50% two years after symptom onset and 3% after 5 years [3]. Although surgical aortic valve replacement (SAVR) reduces symptoms and improves survival in patients with symptomatic AS, it is a Class I recommendation in both European and American guidelines [4,5]. However, SAVR is not performed in approximately 25% of cases due to high surgical risk or significant comorbidities [6]. Transcatheter aortic valve implantation (TAVI) has been developed as a less invasive alternative. Over the last two decades, randomized clinical trials have demonstrated the superiority of TAVI compared to medical therapy in inoperable elderly patients, as well as its non-inferiority compared to SAVR in patients with high to low procedural risk [7,8,9,10,11,12,13,14]. The choice between surgical and transcatheter intervention should be based upon careful evaluation of clinical, anatomical, and procedural elements by the Heart Team (HT), weighing the risks and benefits of each approach for the individual patient [4,5]. In the United States (US), 72991 TAVI procedures were performed in 2019, with an 18% increase compared to the previous year [14]. These data, together with the constant technological improvement in devices, the reduction in peri- and post-procedural complications, and the encouraging results on long-term durability, show that TAVI has become the standard of care for most patients with severe degenerative AS. Healthcare systems should adapt to the raised demand for TAVI interventions in order to avoid increasing waiting times, which translates to a high mortality rate during this period. Indeed, studies performed during the early adoption of TAVI showed that 10–14% of patients died while on the TAVI waiting list [15,16]. The cumulative probability of death and heart failure hospitalization while on the waiting list was 2% and 12% at 80 days, respectively, with a relatively constant rise in event rate with increasing waiting times [17]. A long waiting time for TAVI often leads to deterioration in functional capacity [18,19] and is associated with greater risk in the case of an urgent TAVI procedure [20]. Currently, when a patient with an HT indication for TAVI is admitted to a center without cardiac surgery (CS), there are two main pathways to access the procedure. In the first, the patient is referred to the Heart Valve Center at the time of TAVI. In the second, the procedure can be carried out “in service” in a center equipped with CS by expert operators from the spoke center, who follow the patient throughout the entire process. In both cases, the number of TAVI procedures is limited by the Heart Valve Center’s capacity, leading to an increased waiting list. As an alternative, the procedure can also be performed in hospitals without on-site CS, a condition that represents a paradigm shift in the healthcare system organization of many countries. However, rapidly evolving TAVI technology and increasing operator expertise translate into significantly reduced peri-procedural complications, including emergent cardiac surgery (ECS). As reported in Table 1, in the principal National Registries, there has been a decline in structural complications requiring ECS [14,21,22,23,24], the rate of which is actually less than 0.5%. Furthermore, only a minority of major complications are treated with CS, and the outcome of these patients remains unfavorable, even in an optimal setting comprising on-site CS. As reported in the SOURCE registry, patients undergoing ECS have a mortality rate of 52% at 30 days [22]. In a European multicenter study, of 27760 transfemoral TAVI patients, 212 (0.76%) required ECS. The mortality in this group was 46% during the index hospitalization and 78% at one year [25]. The worst prognosis after ECS was also confirmed in a US study that included 47546 consecutive TAVI patients. In this registry, the in-hospital and 30-day all-cause mortality rate in the surgical bailout group was approximately 50%, which was >10-fold higher than in patients who did not require ECS [26]. In very recent study, including 24,010 patients undergoing TAVR between 2007 and 2022, a 30-day mortality rate of 52% was reported [27]. To support the hypothesis that TAVI without on-site CS is not inferior to TAVI performed in CS hospitals, we performed a meta-analysis of the available studies. The results included 21,173 TAVR patients and indicated that the absence of on-site CS does not increase the risk of early death [28].

The aim of the “TAVI at Home” study is to investigate the feasibility and safety of TAVI in centers without on-site CS, in selected patient populations defined by strict inclusion and exclusion criteria.

## 2. Methods and Analysis

### Study Design

“TAVI at Home” is a single-arm, interventional, multicenter, non-profit study conducted on patients with symptomatic and severe AS with an indication for TAVI through transfemoral arterial access in centers without on-site CS. The study is based on a single-arm design, aiming to evaluate the feasibility and safety of this strategy. The robustness of the data will be strengthened through a multicenter approach. The study was approved by the ethics committee of the Local Health Agency of Romagna (C.E.-ROM) and registered on ClinicalTrials.gov (NCT05886517) on the 2 of June 2023. Indication for TAVI will be given by the HT according to inclusion and exclusion criteria (Table 2). The cardiac surgeon is an important part of the HT; in particular, they are fully involved in the clinical and technical evaluation for proper patient selection. Surgical risk stratification will be performed on all patients using LogEuroSCORE, EuroSCORE II, and STS models for subgroup analysis. Eligibility will be clearly stated on the candidate’s personal record. The cardiac surgeon is requested to provide their opinion on the futility of ECS in the case of severe structural complications. A dedicated clinical interview, involving the clinical cardiologist, the interventional cardiologist, and the cardiac surgeon, will be planned to inform patients about their TAVI indication, the possibility of adhering to the experimental study, and to obtain a signed informed consent form. During the clinical interview, it will be clearly explained to the patient that in case of severe structural complications requiring ECS, the intervention will be deemed futile. 

The study will consist of two phases. A pilot phase enrolling 20 patients (10% of the total expected sample) will be conducted to assess the safety of the procedure. In this phase, a maximum of 4 adverse primary outcome events will be allowed based on the range of variability according to previous data [7,8,29,30].

The pilot phase of this study will be conducted at the Morgagni Hospital, Forlì. Once completed, an interim analysis will be performed by an independent data safety monitoring board. In the second phase, up to 10 centers will be involved to reach the final population of 200 patients. 

The study will be performed according to the Declaration of Helsinki and ICH Good Clinical Practice.

AUSL Romagna will be the study sponsor/promoter and the Istituto Romagnolo per lo Studio dei Tumori (IRST) “Dino Amadori” will be the research partner for the study conduction. Centralized and on-site monitoring of the participating centers is planned to ensure patients’ rights and higher quality of the study results.

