### 3.1. Characteristics of the Centers

Eligible centers must have regular 24 h interventional cardiology activity [33]. The centers must be part of a network where hospitals refer patients to CS centers according to a hub-and-spoke model, in which patients are promptly transferred for ECS in the event of complications. In this model, collaboration between centers with and without on-site CS is crucial for proper patient evaluation and management.

The general requirements are as follows:-An overall procedural volume of at least > 36 TAVI/year (3 TAVI/month preferably > 5 TAVI/month) performed in Heart Valve Centers.-At least two catheterization laboratory rooms, one of which is preferably hybrid.-At least 1000 coronary angiography and 400 percutaneous coronary angioplasty (PCI) procedures per year.-Expertise in percutaneous balloon aortic valvuloplasty procedures.-Expertise in electrophysiology, particularly permanent pacemaker implantation.-A third-level intensive care unit.-A vascular surgery unit on site.

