### 3.5. Outcome Measures

The primary endpoint will be 30-day all-cause mortality, which will be measured as the number of deaths within 30 days of the procedure. Secondary endpoints will include the assessment of technical success and the evaluation of single complications at 30 days after the procedure [32]. Technical success will be defined according to VARC-3 consensus [32]:-Freedom from mortality.-Successful access, delivery of devices, and retrieval of the delivery system.-Correct positioning of a single prosthetic heart valve into the proper anatomical location.-Freedom from surgery or intervention related to the device (excluding pacemaker implantation) or to a major vascular, access-related, or cardiac structural complication.

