## 4. Conclusions

The aim of this study is to evaluate an innovative treatment strategy for patients with severe AS and indications for TAVI. The results are expected to provide prospective evidence on the efficacy and safety of TAVI performed in centers without on-site CS. In addition, extending TAVI procedures to centers without CS could represent a solution to reduce waiting times and ensure continuity of care, particularly for elderly and frail patients, for whom emergency cardiac surgery in the case of severe complications may be futile.

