## Figures and Tables

**Figure 1 jcdd-12-00063-f001:**
[figure not shown]
Study scheme.

**Table 1 jcdd-12-00063-t001:** Conversion to emergent cardiac surgery and principal structural complications after TAVI in principal international registries [14,21,22,23,24]. # 30-day mortality; * in-hospital mortality; ^ 24 h mortality.

	Source (2007–2009)	Source 3 (2014–2015)	France 2 (2010–2012)	France (2013–2015)	Gary (2010–2015)	STS (2011–2019)
N.° of patients	1038	1947	4165	12,557	15,964	276,316
Mean age	81	81	83	83	81	81
LogES (%)	27	18	22	18	18	-
Death (%)	8.5 #	2.2 #	8.1 *	4.4 *	1 ^/5.2 *	2.0 */3.1 #
Conversion to open surgery (%)	2.7	0.6	1.2	0.5	1.3	0.6
Ring rapture (%)	-	0.2	0.3	0.4	0.4	-
Aortic dissection (%)	-	-	0.2	0.4	0.2	-
Coronary obstruction (%)	-	0.4	-	-	-	-
Cardiac tamponade (%)	-	-	1.3	2	1.0	-
Valve malposition (%)	0.3	-	1.3	1.1	-	-
2° Valve implantation (%)	-	0.7	2.3	1.8	-	-

**Table 2 jcdd-12-00063-t002:** Eligibility criteria.

Inclusion criteria - Severe symptomatic aortic valve stenosis - Age ≥ 75 years - Patients evaluated by Heart Team and selected on the basis of at least one of the following criteria: 1. High surgical risk (LogES > 20%, EuroSCORE II > 8%, and STS score > 8%) 2. Porcelain aorta 3. Hostile chest 4. Severe fragility 5. Severe liver disease/cirrhosis 6. Presence of a patent graft of an internal mammary artery crossing midline and/or adherent to the posterior table of the sternum 7. Severe pulmonary hypertension or severe right ventricular dysfunction - Feasible transfemoral access - Signed informed consent form
Exclusion criteria - Aortic valve bioprosthetic dysfunction - Bicuspid aortic valve - Anatomical features associated with an increased risk of major complications: 1. Severe left ventricle outflow tract or sub-annular calcification 2. Valvular ring to coronary ostia distance < 10 mm 3. Severe aortic root dilatation or out-of-range aortic annulus diameters for TAVI - Contraindication for femoral access

**Table 3 jcdd-12-00063-t003:** Thirty-day all-cause mortality after TAVI in patients with high or prohibitive surgical risk [7,8,29,30].

	Partner Trial		STS/ACCTVT Registry	Austrian Registry
	Inoperable	High-Risk	Inoperable + High-Risk	Inoperable + High-Risk
30 Days	(9/179) 5.0%	(12/348) 3.4%	(239/3133) 7.6%	(2/290) 6.9%

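### The consent statement that emergency cardiac surgery will be deemed futile conflicts with the centre requirement of prompt transfer for it, and no rule says which governs

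*Protocol article*

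**What the plan says.** The protocol article speaks about emergency cardiac surgery (ECS) after a complication in four places.

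- **Section 2, Study Design (surgeon's role):** "The cardiac surgeon is requested to provide their opinion on the futility of ECS in the case of severe structural complications".
- **Section 2, Study Design (consent interview):** patients are to be told that "in case of severe structural complications requiring ECS, the intervention will be deemed futile". The sentence has no exception.
- **Section 3.1, Characteristics of the Centers:** eligible centres must belong to a hub-and-spoke network "in which patients are promptly transferred for ECS in the event of complications".
- **Section 4, Conclusions:** TAVI in centres without cardiac surgery is presented as useful for elderly and frail patients "for whom emergency cardiac surgery in the case of severe complications may be futile".

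Two other parts bear on the point. Table 2 admits patients who meet at least one of seven risk criteria, and none of these is a judgement that ECS would be futile. Section 3.5 defines the primary endpoint as 30-day all-cause mortality, "which will be measured as the number of deaths within 30 days of the procedure". It takes technical success from VARC-3, where surgery for a cardiac structural complication counts as a failure.

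**The concern.** The absence of on-site surgery is the feature under test, so what happens when a participant needs surgery is part of the strategy being evaluated. One section tells the patient in advance that surgery will be regarded as futile. Another makes rapid transfer for that surgery a condition of the network in which the centre works. A centre could follow either and cite the protocol.

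Two things are at stake. First, the patient may agree to one pathway and meet another, which touches valid consent and patient safety. Second, the second phase involves up to 10 centres, and they may not handle the same emergency in the same way.

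**Working it through.** **1. The statements side by side**

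| Place | Applies to | Position on ECS |
|---|---|---|
| Study Design, surgeon's opinion | The patient under discussion | Open: an opinion is sought |
| Study Design, consent interview | Every participant | Settled: futile |
| Section 3.1 | Patients in the network; participants not excepted | Prompt transfer for ECS |
| Conclusions | Elderly and frail patients | Conditional: possibly futile |

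- *Consent interview against section 3.1.* For one participant with a severe structural complication requiring ECS, the first calls the surgery futile and the second has the patient moved promptly to receive it. Both cannot describe that patient's care.
- *Within Study Design.* An individual opinion serves a purpose if the answer can differ between patients, yet the consent statement gives one answer for all. The two fit together only if an opinion that ECS is futile is a condition of enrolment.
- *Is it such a condition?* Table 2 does not list it, and section 3 (Study Population) does not mention it. Selection therefore does not remove the conflict, and no other sentence says who is transferred and who is not.

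**2. How many patients would be affected**

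Inputs: n = 200 (section 3.3). The Introduction puts the current ECS rate below 0.5%, and gives 212/27,760 = 0.76% in a European transfemoral study.

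Expected cases = n × r. Probability of at least one = 1 − (1 − r)^200.

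- r = 0.5%: 200 × 0.005 = 1.0 case; 1 − 0.995^200 = 63%.
- r = 0.76%: 200 × 0.0076 = 1.52 cases; 1 − 0.9924^200 = 78%.

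As a sensitivity value, the 1.3% conversion rate of the 2010–2015 registry in Table 1 gives 2.6 cases. The trial excludes anatomies at raised risk of major complications, so the lower figures are the more natural ones.

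**3. An upper bound on the primary result**

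The Introduction reports 52% 30-day mortality and 46% in-hospital mortality after ECS. The article gives no mortality for patients who need ECS and do not have it. I assume 100%, which is an extreme value.

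Extra mortality if surgery is never done = r × (1 − mortality after ECS).

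- Low: 0.5% × (1 − 0.52) = 0.24 points; × 200 = 0.48 deaths.
- High: 0.76% × (1 − 0.46) = 0.41 points; × 200 = 0.82 deaths.

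The standard error at the planned 6.6% is √(0.066 × 0.934 / 200) = 1.76 points, so even the bound is under a quarter of one standard error. The chance of meeting the 10% limit at true mortality 6.6% would fall from 66% to between 57% and 61% with a Wald interval (14 or fewer deaths), or from 44% to between 35% and 38% with an exact interval (12 or fewer deaths). Section 3.3 names no interval method. These falls are ceilings, because they rest on the 100% assumption and on ECS never being done.

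**4. The endpoint definitions**

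All-cause death within 30 days counts each death once, whichever pathway is followed. For technical success, an operated patient fails the surgery component. An unoperated patient who dies at the procedure, receives a second or badly placed valve, or has a percutaneous intervention for the complication fails as well. The score differs only for an unoperated survivor who has a structural complication, no intervention and one correctly placed valve. The article gives no rate for this.

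**The case against.** The strongest reply is that the scopes differ. Section 3.1 describes the network in general and speaks of complications broadly, while the consent statement is confined to severe structural complications. The surgeon's opinion comes just after the eligibility statement, so it may form part of Heart Team selection; a uniform statement to those enrolled would then be coherent. The consent form and the full protocol are not shown, and the event is rare.

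Some of this stands. The scopes do differ, and the selection reading is possible. But section 3.1 sets conditions for study centres, refers to ECS by name and makes no exception for participants, and Table 2 does not support the selection reading. The tension is softened and not removed. Rarity limits the numerical effect, but the consent statement reaches all 200 patients whether or not the event occurs.

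A reader might infer more than the article supports:

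- *That the endpoints contradict each other.* They do not. The primary endpoint is pathway-neutral in its counting, and technical success depends on the pathway only in the rare case described above.
- *That the trial's result turns on this through one particular death count.* Any such threshold assumes an interval method that the article does not name, and the expected shift is below one death even at the bound.
- *That the strategy under test is undefined.* It is defined as transfemoral TAVI in centres without on-site surgery. What is unresolved is one rare branch of it.
- *That patients have in fact consented to something other than their care.* The article only summarises the interview, so a mismatch is possible but not shown.

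**Conclusion.** The concern holds as an inconsistency in the stated rescue pathway. The consent statement, the request for a surgeon's opinion, the centre requirement and the Conclusions take different positions on ECS, and nothing in the article ranks them. The case for correcting it rests on consent, patient safety and uniform conduct across centres, and not on statistical impact. That impact is small: about 1 to 1.5 of 200 patients, and at most about 0.24 to 0.41 percentage points of 30-day mortality.

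These figures assume that the Introduction's ECS rates carry over to this selected population, and the mortality bound also assumes that every patient who needs ECS and does not have it dies. The finding concerns the text of the article. If the full protocol and consent form already state one pathway, only the article's wording is at fault. No view is taken here on which clinical rule is right.

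**What to change.** Reconcile Study Design, section 3.1 and the Conclusions so that the consent statement, the surgeon's recorded opinion and the centre requirement describe one pathway for participants. State whether the surgeon's opinion affects eligibility or what the patient is told. The clinical content belongs to the investigators and the ethics committee. The cost is a wording amendment to the protocol and consent material, best made before further centres join.

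Optionally, record each structural complication for which surgery was considered indicated, whether or not it was performed, and report these descriptively. VARC-3 technical success should stay as defined. This adds one case-report-form item and leaves the sample size and primary analysis unchanged.

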## 3. Study Population

The study population will consists of patients over 75 years of age with severe symptomatic AS with an indication for TAVI. Eligibility will be determined based on a multidisciplinary discussion within the HT, an assessment of the prohibitive surgical risk according to the VARC consensus, or high surgical risk calculated by specific scores [31,32]. The exclusion criteria are contraindications for transfemoral access, aortic valve bioprosthetic dysfunction, bicuspid aortic valve, and instrumental characteristics, evaluated using CT angiography and associated with an increased risk of major complications. All inclusion and exclusion criteria are listed in detail in Table 2. Patients not fulfilling the inclusion criteria or meeting any exclusion criteria will follow the usual organizational pathway, thus undergoing TAVI in a center with CS. Figure 1 shows the study design.

### 3.1. Characteristics of the Centers

Eligible centers must have regular 24 h interventional cardiology activity [33]. The centers must be part of a network where hospitals refer patients to CS centers according to a hub-and-spoke model, in which patients are promptly transferred for ECS in the event of complications. In this model, collaboration between centers with and without on-site CS is crucial for proper patient evaluation and management.

The general requirements are as follows:-An overall procedural volume of at least > 36 TAVI/year (3 TAVI/month preferably > 5 TAVI/month) performed in Heart Valve Centers.-At least two catheterization laboratory rooms, one of which is preferably hybrid.-At least 1000 coronary angiography and 400 percutaneous coronary angioplasty (PCI) procedures per year.-Expertise in percutaneous balloon aortic valvuloplasty procedures.-Expertise in electrophysiology, particularly permanent pacemaker implantation.-A third-level intensive care unit.-A vascular surgery unit on site.

